### Data collection methods

Table 1 shows data collection at the patient, provider, practice, and PHN level.

**Table 1. table1:** Data Source and data collection timepoints

Data source	Practice	Provider	Patient	Primary health network
Tool or survey	*Electronic patient database (PENCS CAT4^TM^*^13^)	Practice survey	NoMAD tool^a^	Interview	Patient survey (all)	Interview	Follow-up SMS survey	Interview	Project timelines
Contact point timeline									
Baseline	X	X							
Post- consultation					SMS link	Telephone			
3 months	X						X	X	X
6 months	X		X				X	X	X
12 months	X		X	X			X		X

SMS = short message service.

a Normalisation Measure Development questionnaire.^17^

### Quantitative instruments

*De-identified patient data from Pen CS CAT4.*^13^ The PHN receives data from all practices in the catchment relating to completion of patient alcohol histories. A data-sharing agreement will be entered into with the PHN and participating practices to access this data. The PHN will provide data on the patients with complete alcohol histories as determined by recording of 'drinker', 'non-drinker', 'nothing recorded', and 'patient <15 years of age with nothing recorded' in the patient’s electronic medical record. The baseline measure will include all active patients; that is, those with at least three visits in the past 2 years. At 3 months and 6 months, the change in proportion of patients with an alcohol history will be measured by comparing the proportion of patients with at least one visit to the practice in the preceding 3 months who had a complete alcohol history. These measures will be available for all other clinics (approximately 850) in the same catchment area for comparison.*Practice survey*. This will be administered at baseline to collect information about the practice’s structure, staffing, record management systems, patient load and demographics, and processes for patient intake and assessment relevant to ABIs.*NoMAD* (Normalisation Measure Development) *tool.^17^* The NoMAD tool is a quantitative survey to be completed by participating GPs, practice nurses, and practice administrative staff to assess how well ABIs were embedded into everyday practice.*Patient survey*. This will be via SMS to capture data on whether patients were asked about alcohol use, how they found the experience, their alcohol use (AUDIT-C),^16^ and demographics including low income status.*Patient survey for patients with risky alcohol use*. Patients who self-report risky alcohol use (AUDIT-C) in the patient survey will be invited to participate in quarterly follow-up SMS surveys. Information will be collected on:

The average weekly consumption of alcohol in standard drinks.The frequency of episodes of high-risk drinking.The number of attendances at the general practice.

A subgroup analysis based on self-reported low-income status will be completed.

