**Method:**

The implementation strategies and resources will be trialled in five general practices over 12 months. The primary outcome will be change in the proportion of adult patients with a complete alcohol history in their electronic medical records. Baseline data collection includes a practice survey to describe practice routines for ABIs and de-identified patient medical record data on completed alcohol histories (repeated at 3, 6, 9, and 12-months post-intervention). Survey and interview data will also be collected from clinicians, patients, and primary health network staff to assess acceptability and feasibility of the intervention.

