### Outcomes

The primary outcome is the change in the proportion of adult patients (aged >15 years) with completed alcohol histories in their electronic medical record. Implementation outcomes, informed by RE-AIM (Reach, Effectiveness, Adoption, Implementation, and Maintenance),^15^ include:

Reach: the change in proportion of patient records with information on alcohol status (drinks alcohol; does not drink alcohol) as a proxy marker for where a brief intervention (BI) is likely to have occurred.Acceptability: to patients, clinicians, practice staff, and PHN staff.Adoption within each practice and within the PHN processes.Fidelity of intervention implementation via project timelines completed by the PHN, research team, and member-checked during provider interviews.Sustainability as perceived by practice staff, clinicians, and PHN staff.

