#### Interrupted time series

An interrupted time series analysis will be performed using data from the enrolled clinics, as well as the 850 clinics within the same catchment to determine how much alcohol screening has changed in the intervention clinics and across whole PHN over the study period.

Analyses will be computed in SPSS (version 24).

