#### Qualitative analysis

Audio files of interviews will be de-identified and professionally transcribed. Analyses will be conducted using NVivo (version 10 or higher).

Although the interview guides will be based on CFIR, inductive thematic coding will be used to ensure the findings are grounded in the data and not a pre-existing framework.

Summarised findings and early interpretations will be discussed with the research team in regular small team meetings. The authors will also meet on a minimum of two occasions with the entire investigator team to finalise the themes from the data.

Table 2 outlines the approach to the mixed-methods analysis of the data.

**Table 2. table2:** Mixed-methods data collection, analysis, and outcomes: implementation matrix adapted from Guetterman *et al*
^19^

**Data type**	**Study aim**	**Data collection procedure**	**Data analysis** **procedure**	**Theoretical framework**	**Products or outcomes**	**Points of integration**
Qualitative	To identify the barriers and facilitators to implementing alcohol BIs in general practice	Interviews: patients; clinicians; practice staff; PHN staff	Inductive thematic coding	CFIRRE-AIM	Perception of implementation processes from multiple viewpoints (acceptability; adoption; fidelity)	Triangulate with NoMAD data to inform implementation process.Compare with practice level data on % alcohol intake recording to look for patterns on increased uptake, or not
Quantitative	Increase uptake of alcohol BIs	Routine data extraction from practice to PHN (drinker, non-drinker, not recorded; sex; age); PHN to share the amalgamated data with research team	Descriptive statistics every 3 months.Interrupted time-series analysis compared with all practices in PHN catchment. Data will be collected monthly	CFIRRE-AIM	% change in patient records with alcohol intake recorded (reach; adoption)	Compare with qualitative interview data to understand barriers and facilitators to % change
Quantitative	To identify the barriers and facilitators to implementing alcohol BIs in general practice	NoMAD survey from practice managers and clinicians	Likert scale	Normalisation Process Theory	Measure of provider assessment of potential 'normalisation' of new procedure (acceptability; adoption; sustainability)	Triangulate with interview data from providers to identify implementation processes

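### The follow-up points for the primary record outcome differ between the Abstract, Table 1 and the operational definition, which stops at 6 months, and no primary time point is named

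*Protocol article*

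**What the plan says.** The Outcomes section states: "The primary outcome is the change in the proportion of adult patients (aged >15 years) with completed alcohol histories in their electronic medical record". It attaches no time point, and no other section supplies one.

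On duration, the Abstract says "The implementation strategies and resources will be trialled in five general practices over 12 months".

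On when the record data are taken, the article speaks in four places:

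- **Abstract, Method:** the record data are "repeated at 3, 6, 9, and 12-months post-intervention".
- **Table 1, captioned "Data Source and data collection timepoints":** the electronic patient database column is marked at baseline, 3, 6 and 12 months. The table has no 9-month row.
- **Quantitative instruments, Pen CS CAT4 item:** "At 3 months and 6 months, the change in proportion of patients with an alcohol history will be measured". This is the only place that says how the change is formed. The baseline denominator is active patients, meaning three or more visits over two years. The denominator at 3 and 6 months is patients seen at least once in the last three months.
- **Table 2, routine data row:** "Descriptive statistics every 3 months", followed in the same cell by the interrupted time series and "Data will be collected monthly".

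**The concern.** These statements concern the primary outcome, and they cannot all be followed. An analyst working from the operational definition would form the change at 3 and 6 months and have no instruction for the second half of the trial. One working from Table 1 would skip 9 months. One working from the Abstract would use four points, two of them without a stated denominator.

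The time point also changes the question. A change at 3 months reflects launch; a change at 12 months says more about whether recording has become routine, which the Method section names as an interest through Normalisation Process Theory. If the two differ, the choice between them decides the headline, and this text does not make it.

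**Working it through.** The article gives no sample size, power or alpha for the primary outcome, so there is no figure to reproduce. The main check is to set the passages side by side.

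| Place | 3 m | 6 m | 9 m | 12 m |
|---|---|---|---|---|
| Quantitative instruments | yes | yes | no | no |
| Table 1, patient database | yes | yes | no | yes |
| Abstract, Method | yes | yes | yes | yes |
| Table 2, descriptive statistics (3-monthly) | yes | yes | yes | yes |

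**Step 1: how the lists relate.** They are nested: {3, 6} lies within {3, 6, 12}, which lies within {3, 6, 9, 12}, which lies within months 1 to 12. Each of the first three lists omits points that the next one includes.

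**Step 2: where the monthly data belong.** Table 2 puts monthly collection beside the interrupted time series and asks for three-monthly description in the same cell. A monthly feed contains every quarterly point, so it does not conflict with quarterly reporting. Its only discrepancy is that Table 1 does not show it.

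**Step 3: is the missing 9-month row deliberate?** The article gives no reason for it. The follow-up text-message survey is called quarterly under Quantitative instruments and three-monthly in Table 2, yet Table 1 lacks a 9-month entry for that source too. This suggests an incomplete table.

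**Step 4: what is undefined at 9 and 12 months.** The rule on recent attenders is written for 3 and 6 months, and baseline uses a different population. For 9 and 12 months the reader cannot tell which denominator applies, so the 12-month change has no stated definition.

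**Step 5: illustration of free choice among time points.** Assume a two-sided 0.05 test at each of k points, which the article does not specify. With independent tests the chance of at least one false positive is 1 − 0.95^k:

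- k = 2: 1 − 0.9025 = 0.098
- k = 3: 1 − 0.8574 = 0.143
- k = 4: 1 − 0.8145 = 0.185

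Simulating equally correlated normal test statistics (400,000 draws) gives 0.090, 0.125 and 0.156 for k = 2, 3 and 4 at an assumed correlation of 0.5, and 0.079, 0.098 and 0.114 at 0.8. With one fixed time point the figure is 0.05.

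**The case against.** The strongest reply has four parts.

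1. **The article condenses a fuller plan.** A full protocol or analysis plan may name the primary contrast. This stands as far as the missing time point goes, and that part would be weak alone. It does not excuse three printed lists that disagree: a later document could choose among them, but this text would still contradict itself.

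2. **The whole course will be reported.** Table 2 commits to three-monthly description, and the time series is meant "to determine how much alcohol screening has changed in the intervention clinics and across whole PHN over the study period". That limits the scope for hiding an unfavourable quarter. It does not say which figure is primary.

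3. **This is a single-arm feasibility study analysed mainly descriptively.** The only 0.05 in the article belongs to the nested text-message survey of 140 patients. The McNemar and Wilcoxon tests are mentioned for repeated measures in general and are not assigned to the primary outcome. This stands, so the error rates above can only be illustrative.

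4. **The Abstract and Table 1 both schedule a 12-month extract.** Also correct. The gap at month 12 is in the rule for forming the change, not in the planned data collection.

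Two stronger readings are tempting. A reader might count the monthly series as a fourth incompatible schedule; Table 2 itself pairs it with quarterly description, so it is not one. A reader might also infer that the plan is set up so that the headline can be picked once the data are in. The documents show only that the text does not exclude this, and nothing in them shows intent.

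**Conclusion.** The point holds as a contradiction about the primary outcome. Three lists of follow-up points disagree, on 9 months in two places and on 12 months in one. The sole operational definition covers only the first 6 of 12 months, and no time point is named as primary.

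The consequence is a definition gap for the longest-term result and an open possibility of selective emphasis. Its size cannot be derived from the document. The range of about 0.10 to 0.14 for three candidate points, or 0.11 to 0.19 for four, rests on an assumed 0.05 test at each point and assumed correlations from 0.8 down to 0. The finding does not depend on those figures. For a mainly descriptive feasibility trial this should be corrected, but it does not undermine the design.

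**What to change.** - In Outcomes, name one primary contrast. The 12-month change is a reasonable choice because it covers the full trial period; the interrupted time-series estimate would serve equally well.
- Use the same patient denominator at baseline and follow-up for that contrast.
- Report the remaining quarters as the trajectory.
- In Quantitative instruments, extend the measurement rule to 9 and 12 months.
- In Table 1, add a 9-month row and show the monthly extracts.
- Check that the Abstract, Table 1 and Quantitative instruments then give the same list.

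The cost is protocol wording. The primary health network already receives these record data from practices in the catchment, so no new data source is needed. If a full protocol or analysis plan already fixes the contrast, it is enough to carry that choice into the three places.

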### Sample size

Five practices will be recruited to evaluate the process of implementation. At least one GP or practice nurse will be formally recruited at each practice; other clinicians will have access to the resources and can participate in team feedback meetings. For the nested short message service (SMS) survey study, 140 patients will be recruited who self-identify as drinking at risky levels across the five practices per the AUDIT-C questionnaire.^16^ The authors are interested in the response rate over time; that is, both the number of responses at each time point, and the number of questions answered at each time point. Changes will also be able to be detected in drinking patterns (10% change total standard drinks per week compared with baseline, power 0.8, significance 0.05).

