#### Patients

The practice will send an SMS to all patients who visited the practice in the previous 3 months, inviting them to fill in a short survey on their experiences of discussing alcohol with their clinician. Patients will also indicate if they are happy to be contacted for a follow-up survey and/or interview. Follow-up surveys will be sent to participants who self-identify as drinking at risky levels.

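### The powered 10% change in weekly drinks has no scheduled baseline; if the selecting survey fills that role, regression to the mean alone can produce a fall of that order

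*Protocol article*

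**What the plan says.** Sample size (protocol article): "140 patients will be recruited who self-identify as drinking at risky levels across the five practices per the AUDIT-C questionnaire". The stated interest is response: "The authors are interested in the response rate over time". The section then adds that a change in drinking will be detectable: "10% change total standard drinks per week compared with baseline, power 0.8, significance 0.05".

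Recruitment, Patients: "The practice will send an SMS to all patients who visited the practice in the previous 3 months". Table 1 puts this survey in its post-consultation row. The baseline row marks only the electronic patient database and the practice survey. The follow-up SMS survey is marked at 3, 6 and 12 months.

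Quantitative instruments: the first patient survey covers whether alcohol was raised, how the patient found it, AUDIT-C and demographics. Then: "Patients who self-report risky alcohol use (AUDIT-C) in the patient survey will be invited to participate in quarterly follow-up SMS surveys". The first item listed for those follow-up surveys is "The average weekly consumption of alcohol in standard drinks", with high-risk episodes and practice attendances after it.

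The Method section describes a single arm. The Quantitative analysis section names McNemar and Wilcoxon signed-rank tests for repeated measures. The roughly 850 other clinics in the catchment supply record-completion data, not patients' drinking.

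**The concern.** The power statement needs a starting value of weekly standard drinks for each patient. On the article's own schedule, that quantity is first measured at 3 months, after selection and after the index consultation. The analyst must therefore do one of two things.

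- **Use the first survey as baseline**, by deriving drinks from AUDIT-C or asking for them at the same time. The same reading then both admits the patient and starts the comparison. People chosen for a high reading tend to read lower next time, and with no patient-level control a within-person test cannot separate that from an effect.
- **Use the 3-month wave as baseline.** This largely removes the selection artefact, but misses any change before 3 months.

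A separate problem pulls the other way. The first survey goes to people who have already attended, so it is not a pre-exposure value. If advice had already lowered drinking, part of a real effect would be hidden.

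The two choices can give quite different answers, and the article does not say which is meant.

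**Working it through.** **1. The planned figure.** For a paired comparison, n = [(z_α + z_power) × SD_change / δ]². The article gives n = 140, δ = 10% of the baseline mean, power 0.8 and significance 0.05. It gives no SD, baseline mean, correlation or sidedness, so 140 cannot be reproduced directly. Solved backwards for a two-sided test:

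SD_change / mean = √140 × 0.10 / (1.960 + 0.842) = 0.42.

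So 140 fits an SD of within-person change equal to 42% of the baseline mean (48% if one-sided). Nothing here shows that 140 is wrong. It shows that the figure depends on a baseline mean that no scheduled survey collects.

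**2. Where weekly drinks are measured.**

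| Contact | Alcohol measure listed | Role |
|---|---|---|
| Baseline row, Table 1 | none from patients | record data and practice survey |
| First SMS survey, post-consultation | AUDIT-C | selects risky drinkers |
| Follow-up SMS at 3, 6, 12 months | weekly standard drinks, high-risk episodes | outcome |

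**3. Size of the no-effect fall if the first survey is the baseline.** None of the following inputs is in the article; all are assumed.

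- Weekly drinks are log-normal with log-SD σ = 0.9.
- Each reading is a stable personal level plus independent occasion error, with retest correlation r = 0.7 to 0.9 on the log scale.
- The AUDIT-C score correlates q = 0.6 to 0.8 with same-occasion log drinks.
- The top share p = 20% to 40% on that score is selected. Let c be the normal cut-off for p.

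With no intervention effect, the ratio of mean drinks at the next reading to mean drinks at the selecting reading is

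Φ(σqr − c) / Φ(σq − c).

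Middle case, p = 30% (c = 0.524), r = 0.8:

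- q = 0.6: Φ(0.432 − 0.524) / Φ(0.540 − 0.524) = 0.463 / 0.506 = 0.915, a fall of 8.5%.
- q = 0.8: Φ(0.576 − 0.524) / Φ(0.720 − 0.524) = 0.521 / 0.578 = 0.901, a fall of 9.9%.

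Extremes:

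- p = 40% (c = 0.253), r = 0.9, q = 0.6: 0.592 / 0.613, a fall of 3.4%.
- p = 20% (c = 0.842), r = 0.7, q = 0.8: 0.368 / 0.452, a fall of 18.6%.

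A simulation of the same model gave 3.5% to 18.6% overall and 8.6% to 9.7% in the middle case, which agrees within sampling error. In simulated studies of 140 patients (300 per scenario), the Wilcoxon signed-rank test at two-sided 0.05 declared a fall in 24% to 99% of studies with no effect.

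**4. Size if the first follow-up wave is the baseline.** Neither this wave nor the next was used for selection. In this model both therefore have the same expected mean, and the ratio is 1. The simulation gave falls of −0.3% to 0.4%, and declared a fall in 1% to 4% of studies.

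**The case against.** **Ancillary analysis.** Drinking change is not among the listed outcomes, and Table 2 gives only response and completion rates as the nested study's analyses. The single arm is openly stated. All this stands and limits the weight of the point. It does not remove the explicit power claim.

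**Condensed article.** The item list of a short survey may sit in a fuller document, and Table 1 is not complete: it has no 9-month row although the follow-up surveys are called quarterly. This is fair, and it weakens any argument from silence. But the article itself gives the instruments, the schedule and the power claim, and as printed they do not fit together.

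**Stronger readings.** A reader might infer that a fall will appear whatever is done. The documents do not support that: the artefact arises only if the selecting survey is the baseline, and the text leaves this open. A reader might also infer that the post-consultation start helps to create a false fall. By itself it would more likely conceal a real one.

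**Assumed inputs.** The share selected, the retest correlation, the AUDIT-C correlation and the log-SD are not document figures. This stands. The range shows that an artefact near 10% is plausible, not that it is expected.

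**Conclusion.** The point holds in a limited form. As printed, the power statement compares weekly drinks with a baseline that the article's own schedule does not collect. What follows depends on how the gap is filled: a no-effect fall of about 3.5% to 18.6%, which spans the 10% target, if the selecting survey is used; about zero if the first follow-up wave is used, provided there is no drift over time or selective dropout. The inconsistency rests on the text alone; the size of the bias rests on the assumptions listed in step 3. Under either choice the starting value follows a consultation and there is no patient-level comparator, so the change cannot be read as evidence of effect. The primary outcome, based on medical records, is untouched.

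**What to change.** 1. Add the weekly-drinks and high-risk-episode items to the first SMS survey, so that every contact uses the same measure.
2. Use AUDIT-C for eligibility only, not as a source of baseline drinks.
3. State in Sample size which survey is the baseline, and align Table 1 with it.
4. Report change from the first follow-up wave, which played no part in selection, beside change from the first survey. Item 1 without this would build in the regression artefact.
5. State that the uncontrolled change is descriptive and is not evidence of effect.

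Comparing patients who were asked about alcohol with those who were not, adjusted for first-survey drinks, would not rescue the analysis. Being asked may precede the value adjusted for and may depend on how much the patient drinks, so the two groups need not regress alike.

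Cost: two more questions in the first survey and some wording. The first survey becomes slightly longer, and change from the first follow-up wave misses any early effect.
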